## LIST OF ABBREVIATIONS AND RELEVANT DEFINITIONS

|         |                                                                                                                                                                                                                                                                                                                                           |
|---------|-------------------------------------------------------------------------------------------------------------------------------------------------------------------------------------------------------------------------------------------------------------------------------------------------------------------------------------------|
| ABR     | ABR form (General Assessment and Registration form) is the application form that is required for submission to the accredited Ethics Committee (ABR = Algemene Beoordeling en Registratie)                                                                                                                                                |
| AE      | Adverse Event                                                                                                                                                                                                                                                                                                                             |
| AR      | Adverse Reaction                                                                                                                                                                                                                                                                                                                          |
| CA      | Competent Authority                                                                                                                                                                                                                                                                                                                       |
| CCMO    | Central Committee on Research Involving Human Subjects                                                                                                                                                                                                                                                                                    |
| CV      | Curriculum Vitae                                                                                                                                                                                                                                                                                                                          |
| DSMB    | Data Safety Monitoring Board                                                                                                                                                                                                                                                                                                              |
| EU      | European Union                                                                                                                                                                                                                                                                                                                            |
| EudraCT | European drug regulatory affairs Clinical Trials GCP Good Clinical Practice                                                                                                                                                                                                                                                               |
| IB      | Investigator's Brochure                                                                                                                                                                                                                                                                                                                   |
| IC      | Informed Consent                                                                                                                                                                                                                                                                                                                          |
| IMP     | Investigational Medicinal Product                                                                                                                                                                                                                                                                                                         |
| IMPD    | Investigational Medicinal Product Dossier                                                                                                                                                                                                                                                                                                 |
| METC    | Medical research ethics committee (MREC); in Dutch: medisch ethische toetsing commissie (METC)                                                                                                                                                                                                                                            |
| (S)AE   | Serious Adverse Event                                                                                                                                                                                                                                                                                                                     |
| SPC     | Summary of Product Characteristics (in Dutch: officiële productinformatie IB1-tekst)                                                                                                                                                                                                                                                      |
| Sponsor | The sponsor is the party that commissions the organization or performance of the research, for example a pharmaceutical company, academic hospital, scientific organization or investigator. A party that provides funding for a study but does not commission it is not regarded as the sponsor, but referred to as a subsidizing party. |
| SUSAR   | Suspected Unexpected Serious Adverse Reaction                                                                                                                                                                                                                                                                                             |
| Wbp     | Personal Data Protection Act (in Dutch: Wet Bescherming Persoonsgegevens)                                                                                                                                                                                                                                                                 |
| WMO     | Medical Research Involving Human Subjects Act (Wet Medisch-wetenschappelijk Onderzoek met Mensen)                                                                                                                                                                                                                                         |

# 1 Summary

## **Rationale and Objective:**

3rd line standard treatment of patients with metastatic colorectal cancer (CRC) harboring K-ras wild type consists of anti-EGFR treatment with either cetuximab or panitumumab. This type of treatment has a modest but significant beneficial activity in this patient group with improved progression-free and overall survival. Although it is well known that patients with advanced CRC harboring a K-Ras mutation will not respond to anti-EGFR treatment, it is not understood why patients with K-Ras wild type CRC do not all benefit from this type of therapy. In order to optimize treatment of these patients as well as health care costs, it is extremely important to identify those patients who will respond to treatment with an EGFR inhibitor at an early stage.

We hypothesize that the differences in response to treatment with cetuximab are due to variability in the pharmacokinetics and -dynamics of the antibody. Thus, we hypothesize that patients who do not respond to anti-EGFR treatment, have insufficient drug levels in tumor tissue. We hypothesize that this is due to pharmacodynamic processes such as sequestration of cetuximab in the liver which expresses high levels of EGF receptor.

With the introduction of immuno-positron emission tomography (PET), an attractive novel option to visualize molecular interactions has been developed using the combination of PET with labeled mAbs. Cetuximab labeled with zirconium-89 (Zr) has been successfully generated (GMP) and is available for this study. Previous studies have shown excellent stability of this compound and Zr is shown to be safe in humans. We will use Zr-cetuximab to demonstrate tumor targeting by imaging and explore the relation of uptake with treatment response. With this approach we hope to achieve a better understanding of the mechanisms of action of this therapeutic mAb in metastasized CRC and eventually develop strategies that may improve efficacy of cetuximab treatment.

**Study design:** Single centre, two step non-randomized intervention study.

**Study population:** Patients with histopathologically confirmed advanced CRC with K-Ras wild type, aged ≥ 18 years, with a life expectancy of at least 12 weeks, who are candidates for anti-EGFR antibody monotherapy (3rd line palliative treatment).

**Intervention:** Patients will be treated with cetuximab. For pharmacodynamic purposes PET-imaging with Zr-labelled cetuximab will be performed. In addition, two [18F]-FDG PET-CT will be performed to explore early response. Patients will undergo blood sampling and two skin biopsies for pharmacodynamic purposes of Zr-labelled cetuximab and kinase activity profiles, respectively.

**Main study objective/endpoint:** The main objective of the first part of the study is the demonstration of Zr-cetuximab uptake in non-hepatic tumor lesions. The main objective of the second part is the association between Zr-cetuximab uptake in non-hepatic tumor lesions and treatment outcome.

**Nature and extent of the burden and risks associated with participation, benefit and group relatedness:** Upon enrolment in this study, patients will be asked to undergo two skin biopsies during treatment. During therapy, follow-up will include standard laboratory analysis, immuno-PET-CT and [18F]-FDG PET-CT on regular visits to the outpatient clinic. Side effects of the medication and adverse events as a consequence of the skin biopsies may occur. The radiation exposure is acceptable and requires no shielding after injection of Zr-labelled cetuximab. Patients may benefit from disease regression or stabilization as cetuximab has proven clinical benefit in this patient population.

## 2 Introduction

### 2.1 Disease information

#### EGFR and colorectal cancer

Colorectal cancer (CRC) is the second cause of cancer death both in the United States and in Europe. In the Netherlands, around 10.000 new patients are diagnosed each year and around 5000 deaths occur annually ([www.ikcnet.nl](http://www.ikcnet.nl)). Recently, therapeutic options have been expanded with the introduction of monoclonal antibodies against the epidermal growth factor receptor, i.e. cetuximab and panitumumab.

Epidermal growth factor receptor (EGFR), a member of the type I receptor tyrosine kinase family, is often upregulated in CRC and this has been associated with tumor aggressiveness and poor prognosis (Goldstein 2001). Activation of EGFR leads to activation of different downstream signaling pathways such as the Ras/Raf/MAP kinase pathway. This pathway plays a key role in the regulation of cell growth, differentiation, proliferation, apoptosis and cellular invasiveness. Activation of the PI3K/Akt pathway is regulated by EGFR as well as PTEN, deficiency of which has been associated with unsuppressed signaling activity (Heineman 2009 and ref therein).

Cetuximab is a chimeric mouse/human IgG1 monoclonal antibody targeted against the extracellular domain of the EGFR. Binding of cetuximab to the receptor prevents ligand binding, induces receptor internalization and causes a direct inhibition of the receptor tyrosine kinase activity (Mendelsohn 2003). Cetuximab may also induce antibody-dependent cell-mediated cytotoxicity (ADCC), but the clinical relevance of this effect is not clear. In several phase II and III clinical trials cetuximab has shown promising efficacy in patients with metastatic CRC, as single agent as well as in addition to chemotherapy (Cunningham 2004, Jonker 2007, van Cutsem 2009, Bokemeyer 2009). However, not all patients benefit. Mutations in downstream targets of EGFR (K-Ras/B-Raf) have been implicated in the resistance to anti-EGFR therapy, i.e. K-Ras mutations have been observed in 40% and B-Raf in 0-12.5% of CRC patients (reviewed in Heinemann 2009). Post hoc analyses are now available which evaluate the influence of K-Ras mutation status on treatment efficacy.

The CRYSTAL trial compared chemotherapy consisting of 5-fluorouracil, folinic acid and irinotecan (FOLFIRI) plus cetuximab to FOLFIRI alone as first-line chemotherapy in metastasized CRC patients. Retrospective analysis revealed that the addition of cetuximab to FOLFIRI caused a significant increase in overall response rate (ORR) in K-Ras wild type patients (43% vs. 59%  $p = 0.0025$ ), while no improvement was observed in the mutant population (40 vs. 36%  $p=0.46$ ) (van Cutsem 2009).

The OPUS trial investigated the 5-fluorouracil, folinic acid and oxaliplatin (FOLFOX) regimen with or without cetuximab in advanced CRC patients. As in the previous trial, cetuximab induced a significant increase in ORR in K-Ras wild type patients (37% vs. 61%  $p 0.011$ ), whereas no effect on ORR was seen in K-Ras mutant patients (49% vs. 33%  $p 0.106$ ) (Bokemeyer 2009).

For pre-treated patients, the literature contains many case-series and posthoc analysis of clinical trials with combining chemotherapy with cetuximab, which all point to the same consistent relation between K-Ras wild type status and response to anti-EGFR treatment in 10-40% of the patients (Benvenuti 2007, Lievre 2008, de Roock 2008). Posthoc analysis of monotherapy cetuximab shows a 12.8% response rate according to RECIST in K-Ras wild type patients (Karapatis 2008). The only prospective study of cetuximab as a single agent in pre-treated metastatic CRC patients showed that K-Ras wild type status was associated with a greater probability of disease control ( $p 0.0003$ ) (Khambata-Ford 2007).

#### Dosage of cetuximab

A critical issue in clinical studies with an EGFR inhibitor is the definition of the optimal biologic dose and schedule. Based on pre-clinical studies, the optimal biological dose was defined as the dose at which EGFR was completely saturated, such that maximal inhibition of tumor growth would be

achieved. It was suggested that complete saturation of EGFR might be associated with a plateau of the systemic clearance of the antibody. Pharmacological analysis of different phase I studies resulted in the recommended loading and maintenance dose every week of 400 mg/m^2 and 250 mg/m^2, respectively (Baselga 2000, Robert 2001, Fracasso 2007). These doses are well tolerated and no DLTs have been observed up to 500 mg/m^2 weekly. A more recent study showed a single DLT with 700 mg/m^2 every two weeks (Tabernero 2009). Interestingly, the trough levels using the recommended dosage varied, and in some patients they were below those estimated to yield saturation (Robert 2001, Tan 2006). At this moment it remains unclear what if any relation exists between trough levels and response.

Recently, biweekly instead of weekly schedules of cetuximab administration, similar to the biweekly schedule of panitumumab, have been assessed in several studies. Biweekly schedules would allow greater flexibility to combine cetuximab with different chemotherapy regimes and result in a significantly decreased burden for patients. These studies show that a biweekly schedule with 500mg/m^2 exhibits similar pharmacokinetics and pharmacodynamics as weekly dosing with 250 mg/m^2 (Taberno 2009, Shitara 2010, Pfeiffer 2008, Martin-Martorel 2008). In addition, safety and efficacy are comparable, making biweekly administration of 500mg/m^2 cetuximab an attractive and effective alternative to the standard weekly schedule.

As a class of targeted drugs, EGFR inhibitors do not show many of the severe side effects commonly observed with cytotoxic chemotherapy except for skin toxicity. Interestingly, a potential association between the severity of skin toxicity and a favorable response to anti-EGFR has been reported. Indeed, skin toxicity is believed to be an 'on target' effect (Cunningham 2004). In addition, hypomagnesemia has been observed after treatment with cetuximab due to blockade of the EGF receptor in the kidney. Recently, it has been suggested that early magnesium reduction after treatment with cetuximab might serve as a marker for efficacy and outcome (Vincenzi 2008). Despite these observations, at this moment in time it is still unclear which patients may benefit from treatment with cetuximab and who will not, and ways to identify treatment failure in a timely fashion are urgently needed.

## **2.2 Immuno-PET**

The introduction of immuno-positron emission tomography (PET), the combination of PET with mAbs, is an attractive novel option to visualize molecular interactions. In advanced CRC patients, treatment with cetuximab labeled with a positron emitter has the potential for quantification of the interactions of the drug within the different compartments of the body, including metastases. The positron emitters Zr ( $t_{1/2} = 78.4$  h) is particularly well suited for imaging of slow kinetic intact antibodies because its long half-lives allows imaging at late time points for obtaining maximum information. VUmc has obtained a leading position in immuno-PET imaging by the introduction GMP (good manufacturing practice)-compliant procedures for the production and purification of positron emitters like Zr, by the development of universal procedures for stable coupling of this positron emitters to MAb, and by performing preclinical and clinical safety and proof of principle studies. There is no shielding required and the patient can go home directly. The first two days, the patient is not allowed in the proximity of children and pregnant women. Additional information regarding Zr cetuximab can be found in SECTION 6.

## **2.3 Study rationale**

Although it is well known that most patients with advanced CRC containing a K-Ras mutation will not respond to anti-EGFR treatment (Amado 2008, van Cutsem 2008, Bokemeyer 2008), it is unknown why not all patients with K-Ras wild type benefit from this type of therapy. Although mutations in other downstream signaling molecules (e.g. BRAF) may play a role, this does not explain it completely (di Nicolantonio 2008).

We hypothesize that differences in response to cetuximab treatment in patients with wild type K-Ras CRC are primarily due to variability in the pharmacokinetics and -dynamics of the antibody. Thus, we hypothesize that patients who do not respond to anti-EGFR treatment, have insufficient drug levels in tumor tissue. We hypothesize that this is due to pharmacodynamic processes such as sequestration of cetuximab in the liver which expresses high levels of EGF receptor.

Based on this hypothesis we have designed a two step exploratory pilot immuno-PET study for patients with metastasized, K-Ras wild type CRC who will be treated with cetuximab. In the first part, we will aim to demonstrate targeting of  $^{89}\text{Zr}$ -cetuximab to non-hepatic tumor lesions. In vivo imaging in tumor-bearing mice has shown promising results regarding imaging the tumor lesions with  $^{89}\text{Zr}$ -cetuximab (Aerts et al 2008). Previous studies have shown  $^{89}\text{Zr}$  to be safe in humans (Borjesson 2006).

After having demonstrated uptake of  $^{89}\text{Zr}$ -cetuximab, we will proceed to the second part of the study and assess the association between tumor uptake and response. Our aim will be to identify those patients that fail to show clinical benefit (i.e. complete response, partial response and stable disease according to RECIST 1.1 criteria). If this pilot study reveals that indeed cetuximab has an inter-patient differential pharmacokinetic profile with insufficient tumor homing associated with lack of response, we have planned a dose finding follow-up study using increasing cetuximab doses until tumor lesions are sufficiently targeted based on immuno-PET imaging.

## 3 Objectives of the trial

### 3.1 Objectives

#### 3.1.1 Part one - Primary objective

3.1.2 To demonstrate uptake of  $^{89}\text{Zr}$ -cetuximab in non-hepatic tumor lesions using immuno-PET when administered during the loading dose of cetuximab.

#### 3.1.3 Part two - Primary objective

To investigate whether there is an association between uptake of cetuximab in non-hepatic tumor lesions and response according to RECIST 1.1 criteria.

#### 3.1.4 Part two - Secondary objectives

- 1) To investigate whether there is an association between levels of uptake of  $^{89}\text{Zr}$ -cetuximab in the liver compared to levels of uptake in non-hepatic tumor lesions.
- 2) To explore whether the response observed on [18F]-FDG-PET can serve as an early response marker for future response to targeted therapy according to RECIST 1.1.
- 3) To explore whether there is an association between  $^{89}\text{Zr}$ -cetuximab uptake in non-hepatic tumor lesions, grade of skin toxicity and response according to RECIST 1.1.

### 3.2 Endpoints

#### 3.2.1 Part one - Primary endpoint

The detection of  $^{89}\text{Zr}$ -cetuximab uptake in non-hepatic tumor lesions (present/absent; present being defined as levels measured in ROI's > standard deviation of background +1).

#### 3.2.2 Part two – primary endpoint

The % uptake (of total injected)  $^{89}\text{Zr}$ -cetuximab in non-hepatic tumor lesions as measured in ROI's corrected for background levels.

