### 5.5.2 Immuno-PET acquisition

All PET studies will be performed on a Gemini TF-64 PET-CT scanner. In 5 patients, whole-body PET scans (trochanter major femora-skull vertex) will be acquired after a single injection of 37 MBq  $^{89}\text{Zr}$ - cetuximab on day 1 (0-2h after injection), day 2, 3, 4 and 7 for pharmacokinetic purposes. In the remaining patients, PET scans will be acquired on day 1 and day 4 or 7 depending on the optimal time point determined with the results of the first five patients. The venous infusion line inserted for administration of unlabelled cetuximab will be used for  $^{89}\text{Zr}$ - cetuximab injection as well. At each scan a second venous cannula will be inserted for blood sampling. Blood samples will be used to measure absolute radioactivity concentration in whole blood and plasma. Prior to each whole-body PET scan, a 30 mAs low-dose CT scan will be acquired for attenuation correction and localization purposes. PET scans will consist of 10-12 bed positions, depending on the length of the patient, of 5 min each. Total acquisition time per scan, including LD-CT, will be below 90 min.

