### 5.5.3 Data-analysis $^{89}\text{Zr}$ - cetuximab scans

All PET data will be corrected for dead time, scatter, randoms, decay, tissue attenuation. PET/CT data will be reconstructed with TF-OSEM, resulting in a transaxial spatial resolution of ~7 mm in the centre of the field of view. Regions of interest (ROIs) will be defined using the CT images which are co-registered to the PET/CT data. ROIs around the organs which accumulate  $^{89}\text{Zr}$  (e.g. liver, lung, and metastatic lesions) will be drawn manually directly on the PET images. All tissue concentrations will be related to the blood concentration. The radioactivity concentrations in all regions for all imaging time points should be recorded digitally in a spread sheet. A tumor lesion will be scored positive if there will be uptake above background, being defined as  $\text{SD}(\text{background}) + 1$ .

For pharmacokinetics, absorbed dose calculations will be made using the Olinda/EXM 1.0 software package, based on the Medical Internal Radiation Dose scheme (Stabin 2005).

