## 7 Statistical considerations

### 7.1 Evaluation - type of variable

1. Uptake of  $^{89}\text{Zr}$ -cetuximab in non-hepatic tumor lesions (present/absent)
2. Uptake of  $^{89}\text{Zr}$ -cetuximab in non-hepatic tumor lesions (% of total dose injected) (continuous)
3. Uptake of  $^{89}\text{Zr}$ -cetuximab in liver (% of total dose injected)
4. Response according to RECIST 1.1 (categories)
5. Response according to % change of non-hepatic tumor lesion long axis / lymph node short axis
6. [18F]-FDG  $\text{SUV}_{\text{max}}$
7. Grade skin toxicity
8. Serum magnesium level

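### The Part two uptake endpoint is a share of injected activity not normalised for lesion volume, so it is confounded with lesion size and does not match the drug-level hypothesis

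*Protocol*

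**What the plan says.** Protocol 3.2.2 gives the Part two primary endpoint as "The % uptake (of total injected") in non-hepatic tumour lesions, "as measured in ROI's corrected for background levels". Item 2 of section 7.1 lists the same variable: uptake "in non-hepatic tumor lesions (% of total dose injected) (continuous"). Under the secondary endpoints of 7.2.2, items 1, 2 and 4 analyse it against change in tumour axis, liver uptake and skin toxicity grade. None of these places divides by volume or mass, or says how several lesions become one value per patient.

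The hypothesis, in the Summary and in 2.3, is that non-responders "have insufficient drug levels in tumor tissue".

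Section 5.5.3, on scan analysis, works in concentrations: "All tissue concentrations will be related to the blood concentration", and "The radioactivity concentrations in all regions for all imaging time points should be recorded digitally in a spread sheet". It does not say that the endpoint is calculated from these values.

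The primary comparison in 7.2.2 is of binary data between patients with disease control and patients with progression. It gives no cut-off on percentage uptake. The only present/absent rule in the protocol is the above-background rule in 3.2.1 (Part one) and 5.5.3.

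**The concern.** Drug level in tissue is a concentration. The share of injected activity found in a region is that concentration multiplied by the region's volume. Two patients with the same tumour concentration can therefore have very different endpoint values, and a large lesion with poor targeting can outscore a small lesion with good targeting. The trial wants to know whether poor targeting goes with treatment failure, so size variation enters the marker as noise. If lesion size is itself related to outcome, it also enters as bias. Section 4.1 requires a measurable lesion outside the liver and sets no upper size limit, so nothing in the eligibility criteria holds size constant.

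**Working it through.** **1. The plan's own figure.** Inputs from 7.2.2: rates 0.7 and 0.2, type I error 0.1, power 0.9, 1.5 controls per case. The pooled rate is (0.7 + 1.5 × 0.2)/2.5 = 0.4. Two-sided, without continuity correction:

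cases = [1.645 √(0.4 × 0.6 × (1 + 1/1.5)) + 1.282 √(0.7 × 0.3 + 0.2 × 0.8/1.5)]² / 0.5² = (1.040 + 0.721)²/0.25 = 12.4, so 13.

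Controls are 1.5 × 13 = 19.5, so 20, and the total is 33 against the stated 35. With 14 + 21 = 35, the two-sided Fisher test has exact power 0.907. The figure stands. It rests on binary rates, so the uptake unit does not alter it.

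**2. What the endpoint measures.** With concentration C, background B, volume V and injected activity A (one planned value, 37 MBq, in 5.5.2):

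- % injected = 100 × C × V / A, or 100 × (C − B) × V / A after subtracting background. V remains in both.
- For a sphere, V = (π/6) d³, so at equal C and B the endpoint scales with d³.

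Illustrative diameters (not from the protocol):

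- 4 cm against 2 cm: (4/2)³ = 8-fold.
- 3 cm against 1 cm: 27-fold, and still 13.5-fold if the larger lesion has half the concentration.
- 6 cm against 1.5 cm: 64-fold, a deliberately wide contrast.

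**3. How far size dominates.** On the log scale, log(% injected) = log C + 3 log d + constant. If size is independent of concentration and C is lognormal, the share of variance due to volume is Var(3 log d) / [Var(3 log d) + ln(1 + CV²)]. All spreads here are assumptions, because the protocol gives none.

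- Diameter uniform 1–5 cm, CV 0.3: 1.715/(1.715 + 0.086) = 95%.
- Diameter uniform 1.5–4 cm, CV 0.8: 0.688/(0.688 + 0.495) = 58%.
- Diameter uniform 1.5–4 cm, CV 1.5: 0.688/(0.688 + 1.179) = 37%.

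**4. What this could do to the primary test.** Assume that cases have twice the controls' concentration, CV 0.5, one lesion per patient, size independent of both concentration and outcome, and a cut-off at which 20% of controls are positive.

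- On concentration: AUC 0.85. The case rate is Φ(0.693/0.472 − 0.842) = 0.73, and Fisher power with 14 v 21 patients is 0.94.
- On % injected, simulated with diameters uniform over 1–3, 1–5 or 1.5–4 cm: AUC 0.64 to 0.69, case rate 0.41 to 0.46, power 0.31 to 0.43.

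This loss is pure dilution. It applies only if the binary variable is a cut-off on % injected.

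**The case against.** The strongest reply is that the primary test is binary and the protocol's only present/absent rule is a level above background, which volume does not enter directly. That stands as far as it goes, but 7.2.2 does not say that this rule is meant. If it is, the endpoint declared in 3.2.2 is not what the primary test analyses. Either way the text needs correction, and the continuous analyses remain exposed.

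A second reply is that this is an exploratory pilot and concentrations are recorded anyway, so a per-volume measure can be calculated later. That makes the repair cheap. It does not make the stated unit right, and choosing the unit after seeing the data is what a stated endpoint should prevent. Nor is this detail left to an analysis plan, since the protocol itself fixes the unit.

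A reader might infer more than the documents support:

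- That the endpoint measures size instead of drug level. It is the product of both, and which dominates depends on unknown spreads.
- That larger tumours in progressing patients would reverse the association. This is possible, but the protocol gives no relation between burden and outcome.
- That lesions are summed, adding total burden. No section says so; the combination rule is simply unstated.
- That 5.5.3 is a rival endpoint definition. It describes processing and recording, and the defect is that it is never linked to the endpoint.

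**Conclusion.** Wrong as written. The endpoint unit in 3.2.2, repeated in 7.1 and used in items 1, 2 and 4 of the secondary analyses, is confounded with lesion size and does not match the stated hypothesis. The scaling with volume follows from the definition, and the 8-fold example needs only equal concentration and spherical shape. The variance shares (37% to 95%) and the fall in power (0.94 to 0.31–0.43) rest on assumed lesion sizes and concentration spreads and are illustrations, not estimates for this trial. The secondary analyses are affected on any reading; the primary test is affected through volume only if percentage uptake is dichotomised. The sample size is not in question here.

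**What to change.** In 3.2.2, in 7.1 item 2 and in secondary analyses 1, 2 and 4 of 7.2.2, define non-hepatic tumour uptake per unit volume. Name one primary measure in advance, for example SUV or % injected dose per mL calculated from the concentrations recorded under 5.5.3. The tumour-to-blood ratio can serve as a sensitivity analysis; it also varies with the blood level, so it is not interchangeable with the other two. State one rule for combining a patient's non-hepatic lesions into a single value. In 7.2.2, state that the binary uptake variable is derived from this measure, and how.

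The cost is wording: no new scan, patient or sample-size calculation. There is one small downside. Section 5.5.3 gives a resolution of about 7 mm and lists no partial-volume correction, so concentration in small lesions may read low. Add a sensitivity analysis that excludes lesions below a size fixed beforehand.
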